
### ***Simulation Scenarios.***

Prior to each scenario, all participants will don personal protective equipment (PPE), consisting of: a gown, nitrile gloves, face shield, goggles, and a N95 respirator (see budget). The brand, type and size of gowns and face shields will be standardized across all sites. PPE will be donned with a partner, guided by a standardized PPE donning checklist, and checked by a research assistant prior to the scenarios. All scenarios are 5 minutes in duration and tightly standardized by using a scenario template with pre-scripted patient progression. Intervention arm teams will use the aerosol box in all three scenarios while control arm teams will not use the aerosol box. At the end of the entire session, participants will receive an educational debriefing to discuss performance issues, infection control measures, and technical skills using a blended-method approach to debriefing. Doffing will occur in conjunction with a PPE partner, and guided by a standardized PPE doffing checklist to ensure consistency.

*Scenario A: BVM Ventilation* - depicts an adolescent patient with suspected COVID-19, presenting with progressive respiratory distress and desaturation. Participants will be directed to initiate BVM ventilation with a HEPA filter as per guidelines for managing COVID-19 pediatric patients. Aerosolization of particles occurs during manual ventilation, while the mask is on the patient's face. The scenario will last a total of 5 minutes.

*Scenario B: ETI* - depicts a patient with suspected COVID-19, presenting with progressive respiratory failure requiring intubation. In this scenario, providers will be advised by the team leader not to initiate BVM ventilation, which is consistent with AHA guidelines for adult COVID-19 patients requiring airway management. Participants will be directed to sedate, paralyze and intubate the patient using a videolaryngoscope (e.g. GlideScopeTM), and provide manual ventilation after intubation with a HEPA filter in place. The scenario will last a maximum of 5 minutes, or until the patient is successfully intubated, whichever is longer.

*Scenario C: LMA Insertion* - depicts the same patient as in Scenario B. In this scenario, providers will be advised by the team leader to insert an LMA. Participants will be directed to sedate, paralyze and intubate the patient, and provide manual ventilation after LMA insertion with a HEPA filter in place. The scenario will last a maximum of 5 minutes, or until the patient is successfully intubated, whichever is longer.

Data collection will occur immediately after each scenario, prior to and after doffing of PPE (see outcomes below). After data collection, the resuscitation room and airway trainer will be cleaned. Clean PPE will be provided for all participants for each scenario. These measures will ensure there is no incremental accumulation of GloGermTM particles from prior scenarios. All scenarios will be videotaped from a birds-eye view angle at the foot of the bed.

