***Simulating Aerosolization.***

The amount of aerosolization that occurs in real patients is highly variable and dependent upon many factors (e.g. viral load, method of aerosolization, etc.), making it impossible to exactly replicate aerosolization of SARS-CoV-2 virus in the simulated environment. In our study, we aim to create a model of aerosolization by standardizing various aspects of care (e.g. ventilation pressures, particle size and volume deposited, lung compliance), thus allowing us to make comparisons between different contexts (ie. aerosol box vs no box; BVM vs. LMA vs. ETI). To visualize aerosolization of particles, we will adapt methodology successfully utilized by members of our research team in studies evaluating aerosolization during airway management. GloGerm™ (Glo Germ Company, Moab, UT, USA) is a nontoxic, invisible fluorescent resin marker that illuminates when exposed to ultraviolet (UV) light. The SARS-CoV-2 virus requires a water and mucus envelope to spread, with the size of these virus-containing envelopes varying from larger droplets ( $>60\ \mu\text{m}$ ) to smaller airborne particles or infectious droplet nuclei ( $5\text{-}10\ \mu\text{m}$  diameter). With a particle size of approximately  $1\text{-}5\ \mu\text{m}$ , Glo Germ™ represents a reasonable surrogate for aerosolized SARS-CoV-2. AGMPs can generate aerosols in two ways: by mechanically inducing and dispersing aerosols, or by inducing the patient to cough to produce aerosols. Our study focuses on aerosols mechanically induced by three commonly performed AGMPs: BVM ventilation, LMA insertion, and ETI. Glo Germ™ (0.5 mL) will be applied to the oropharynx and trachea of the manikin to simulate secretions. Glo Germ™ will be aerosolized from the mechanical pressures and airflow associated with bagging, or from manipulation of the airway, which is consistent with the current understanding of aerosolization mechanics in AGMPs. Participants will titrate ventilation pressures to 20 cm H2O peak inspiratory pressure, and 5-6 cm H2O peak end expiratory pressure using a digital pressure manometer that provides real-time feedback. Pilot work done by our research team using the methods (and ventilation pressures) described above resulted in contamination on the hands, torso, face shield, and feet of airway providers during BVM ventilation. This suggests these methods are sufficient to produce a measurable amount of Glo Germ™ particles during manual ventilation.

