## **2.8, 2.9 Outcome measures.**

Primary outcome: Surface area of contamination (AOC) quantified from digital photos of GloGerm™ deposited on the airway team members pre and post-doffing. A digital reference grid will be applied over each photo, with mean grey values of areas within each grid “pixel” calculated using Image J (NIH) software. As areas highlighted by GloGerm™ will illuminate more brightly, mean grey value per pixel will be the base unit to quantify degree of contamination relative to the provider’s anatomic surface area. This quantitative measure permits comparative analysis between groups or scenarios, and is congruent with accepted measures in the bioimaging informatics, digital immunohistochemistry, and direct immunofluorescence. Digital images of participants will be captured in a standardized fashion under UV-illumination in a fashion to minimize confounders (brightness, angle, lighting) (see budget). Images will be taken pre- and post-doffing to capture extent of contamination on PPE (pre) and extent of contamination on provider surfaces underneath PPE.

Secondary outcomes: (a) time to successful intubation or LMA insertion (captured by video review by 2 trained and calibrated raters); (b) first pass success rate for ETI and LMA insertion (captured by video review by 2 trained and calibrated raters).

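### Cleaning the room and replacing PPE does not reset the surfaces on which post-doffing contamination is measured, so later scenarios may carry tracer from earlier procedures

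*Protocol*

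**What the plan says.** Each team does three scenarios in sequence, in random order (protocol 2.1), on one day (2.6, 2.7). Section 2.2 (Simulation Scenarios) sets the imaging times: "Data collection will occur immediately after each scenario, prior to and after doffing of PPE". Two measures then separate one scenario from the next: "After data collection, the resuscitation room and airway trainer will be cleaned", and "Clean PPE will be provided for all participants for each scenario". From these two alone the protocol concludes: "These measures will ensure there is no incremental accumulation of" tracer from earlier scenarios. The conclusion is not limited to the pre-doffing measurement.

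Section 2.8, 2.9 defines the primary outcome as contaminated area "quantified from digital photos of GloGerm™ deposited on the airway team members pre and post-doffing". The post-doffing image is meant to show the "extent of contamination on provider surfaces underneath PPE".

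The PPE is "a gown, nitrile gloves, face shield, goggles, and a N95 respirator", with no foot cover listed. Pilot work (2.2, Simulating Aerosolization) found "contamination on the hands, torso, face shield, and feet of airway providers during BVM ventilation".

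Section 2.16, 2.17 compares the arms by procedure with rank-sum tests and analyses pre- and post-doffing contamination separately.

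**The concern.** New PPE gives a clean start to what is photographed before doffing. It does nothing to the skin and clothing photographed after doffing, and those belong to the same two people in all three scenarios. The protocol names no cleaning of participants, no UV check before the next donning and no baseline image. The guarantee therefore does not cover one of the two components of the primary outcome. Before doffing, the feet may be affected in the same way.

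If tracer reaches those surfaces and stays, a later scenario's post-doffing value contains part of what earlier procedures deposited. Wherever the box reduces contamination, the control arm carries more forward. A box effect in one procedure can then appear in the test for another, and differences between procedures shrink. This matters because section 2.2 presents the aerosolization model as a basis for comparing the three procedures as well as box with no box, and section 2.16, 2.17 tests by procedure. Random order spreads carry-over evenly over the procedures on average, but does not remove it.

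**Working it through.** **Which surfaces are reset.**

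| Image | Surface | Reset by a stated measure? |
|---|---|---|
| Pre-doffing | Gown, gloves, face shield, goggles, respirator | Yes, replaced |
| Pre-doffing | Feet (tracer found in pilot, no cover listed) | None stated |
| Post-doffing | Provider surfaces under the PPE | None stated |

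**The plan's own figure.** The calculations below use the 30 teams per arm and correlation of 0.7 from section 2.10. With d = 0.65, power 0.8 and two-sided alpha 0.05 (sidedness assumed), n = 2 × ((1.960 + 0.842)/0.65)² = 37.15 per arm. Three repeated measures multiply this by (1 + 2 × 0.7)/3 = 0.80, giving 29.72, or 30 after rounding up. The figure reproduces and is not in dispute.

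**Carried share.** Let p be the fraction of tracer on a surface that is still there at the next post-doffing image. The documents give no value, so a range is shown. The model is

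measured(k) = deposit(k) + p × measured(k−1).

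With equal deposits of 1, positions 1, 2 and 3 read 1, 1 + p and 1 + p + p². The mean is 1 + (2p + p²)/3, and the carried share is 1 − 1/mean.

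| p | Positions 1, 2, 3 | Mean | Carried share |
|---|---|---|---|
| 0 | 1, 1, 1 | 1.00 | 0% |
| 0.25 | 1, 1.25, 1.31 | 1.19 | 16% |
| 0.5 | 1, 1.5, 1.75 | 1.42 | 29% |
| 1 | 1, 2, 3 | 2.00 | 50% |

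**Contrast between procedures.** Over the six orders, any other procedure comes immediately before a given one in 2 of 6 and two places before in 1 of 6. Its deposit therefore enters with weight p/3 + p²/6. Take illustrative true deposits of 3, 2 and 1. At p = 1 the weight is 0.5, so the highest reads 3 + 0.5 × 3 = 4.5 and the lowest 1 + 0.5 × 5 = 3.5. The true ratio of 3.0 becomes 1.3; at p = 0.5 it is 1.8, and at p = 0.25 it is 2.2.

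**Effect on one procedure's test.** This was simulated with log-normal deposits, total log SD 1 (assumed), correlation 0.7, 30 per arm, random order and a rank-sum test. The box lowers BVM and ETI deposits by log 1 or log 2 (1 − e⁻¹ = 63%, 1 − e⁻² = 86%) and leaves LMA unchanged. Rejection for LMA, nominal 5%:

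| p | 63% reduction | 86% reduction |
|---|---|---|
| 0.25 | about 7% to 9% | about 9% to 10% |
| 0.5 | 10% | 21% |
| 1 | 22% | 44% |

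With no box effect in any procedure, rejection stays at 4% to 6% at every persistence tried.

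**Candidate corrections.** Subtracting the preceding post-doffing image leaves deposit(k) − (1 − p) × measured(k−1). That is right only at p = 1. Otherwise it takes away too much, and more in the arm with the larger earlier deposits. In the same set-up, LMA rejection is 34% and 50% at p = 0.5, and 50% and 78% at p = 0, essentially always with the box looking worse. A baseline taken just before donning removes p × measured(k−1) and leaves deposit(k). That analysis and a first-scenario-only analysis both stay near 5%.

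**The case against.** Five points can be made for the plan.

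- **Silence is not proof.** The protocol does not say that participants go uncleaned. The doffing checklist (2.2) and the standard operating procedures (2.12) are not shown and could include washing. This stands, and is why the point says may include. It does not rescue the guarantee, which rests only on the room, the manikin and the PPE.
- **The trial remains a fair comparison.** A reader might infer that the post-doffing tests are invalid or that the procedure-specific conclusions are wrong. The documents do not support that. Order is random, both arms do all three scenarios, and the test holds its level if the box has no effect anywhere. The 22% to 44% needs full persistence and a box that works strongly in two procedures and not at all in the third. The stated hypothesis (1.2) is a general reduction. With a common log effect of 0.65, carry-over only lowers LMA power, from about 70% to 64% at half persistence or 59% at full persistence.
- **Tracer may seldom get under the PPE.** If 80% of those deposits are zero (also an assumption), the LMA test rejects in 5% to 7% at persistence from 25% to 100%. This stands as a limit on size.
- **The pre-doffing outcome is largely protected.** This also stands. Hands, torso and face are behind items that are replaced. Only the feet have support in the protocol, and it does not say what the pilot providers wore. Nothing reports tracer on hair or neck.
- **Random order deals with it.** It balances position on average, but each procedure's value still mixes in the others.

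**Conclusion.** The no-accumulation statement is wrong as written for the post-doffing component of the primary outcome, and possibly for the feet before doffing. The consequence is limited to attribution: a procedure's post-doffing result may reflect other procedures, and contrasts between procedures may be diluted. It should not be read as showing that carry-over will occur, that the overall box comparison is invalid, or that the pre-doffing results are generally compromised.

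The size is conditional. It rests on unknown persistence, on tracer reaching the surfaces under the PPE, on an assumed log SD of 1 and, for the inflated rejection rates, on a selective box effect. It ranges from negligible, if little tracer gets under the PPE or stays there, to half of the average measured value at full persistence. The planned sample size is not affected. The matter should be settled before recruitment, because a missing cleaning step or baseline image cannot be supplied afterwards.

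**What to change.** 1. In section 2.2, limit the no-accumulation statement to the PPE surfaces that are replaced.
2. Immediately before each donning, either clean participants' exposed skin and footwear and confirm under UV that no tracer is visible, or take a UV baseline image set and analyse the increase over that image. If the operating procedures already require cleaning, say so in the protocol.
3. Report post-doffing results from each team's first scenario only, as a sensitivity analysis.
4. Do not use the preceding post-doffing image as the baseline. Tracer lost between scenarios would bias the comparison against the box.

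The cost is a few minutes and, for the baseline option, one photo set per scenario. Subtracting images adds some noise, and tracer lost during the scenario itself would not be corrected. The first-scenario analysis uses about one third of the data, or about 30/3 = 10 teams per arm for each procedure, so it can show whether the results agree but is imprecise by itself.

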### ***2.3 Randomization method.***

Randomization will occur at the level of the team, stratified by study site and sex of the airway provider (to ensure equal distribution of sex in both arms), and conducted in blocks of 4 to ensure an even distribution of teams across study arms. Randomization packages will be prepared at a central study site using a web-based random number generator. Sequentially numbered recruitment packages provided for each site will contain sealed opaque envelopes (i.e. one envelope per study arm) with study arm assignments and unique identifier codes for participants.

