## **2.0 THE PROPOSED TRIAL**

### ***2.1 Trial design.***

We plan to conduct a prospective, randomized controlled trial at four INSPIRE network sites (Alberta Children's Hospital, Ste. Justine Hospital, and Children's Hospital of Los Angeles and The Hospital for Sick Children). Simulation-based research confers the advantage of answering research questions without risk of harm to HCPs or patients, which is particularly important when studying a disease process with high mortality. Ethics approval has been submitted at all sites. Two participants will form an airway team, recruited to play the roles of airway provider and airway assistant for management of a simulated, critically ill COVID-19 patient. Participants will be randomized by team into either the control arm (i.e. no aerosol box) or the intervention arm (i.e. use of aerosol box) (Figure 2). Following randomization, all participants will view a short video orienting them to the simulated clinical environment. Intervention arm teams will view an additional video orienting them to the use of the aerosol box, and receive up to 15 minutes of hands-on training (see below for details). After orientation, teams will participate in three sequential simulation scenarios. The order of scenario delivery will be randomized to eliminate scenario order as a potential confounder. The location and nature of equipment, temperature and humidity within the resuscitation room will be standardized across all sites. A Laerdal Resusci-Anne manikin will be used as a simulated patient.

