## **2.10 Sample size.**

Sample size estimation is based on primary outcome measure. Given the paucity of quantitative research in this area, we propose a sample of 60 teams (120 participants) in total, or 30 teams (60 participants) per study arm. As each team will receive repeated measures (i.e. 3 scenarios), this sample size allows us to detect a medium effect size (Cohen’s  $d = 0.65$ ), with a significance level of 0.05, a power of 0.8, and a high intra-cluster correlation coefficient ( $\rho = 0.7$ ) to make a conservative estimation. Accounting for missing data due to technical issues, we will recruit 2 extra teams per study group, resulting in a total sample size of 64 teams (128 participants).

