### **2.16, 2.17 *Statistical analysis.***

Demographic characteristics of participants including sex, profession, years of clinical experience and other identifiers (e.g. height, body surface area) will be reported using descriptive statistics between 2 study arms. For the primary outcome, assuming non-normal distribution of data, we will use Wilcoxon rank sum tests to compare the AOC in 3 different procedures in both airway providers and assistant roles. Analyses to evaluate the degree of contamination pre- and post-doffing of PPE will be conducted separately. Time to procedural completion and first pass success rates will be compared with the Wilcoxon rank sum tests.

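### Randomisation is stratified by site and airway-provider sex, but the planned rank-sum tests for contamination and procedure time use neither; if these factors predict outcome, each test is conservative and forgoes power

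*Protocol*

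**What the plan says.** Protocol section 2.1 describes a "prospective, randomized controlled trial at four INSPIRE network sites". Under section 2.3, teams are randomised "stratified by study site and sex of the airway provider", and this is "conducted in blocks of 4 to ensure an even distribution of teams across study arms". The reason given for stratifying on sex is balance between arms.

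For the primary outcome, area of contamination (AOC), section 2.16 says "we will use Wilcoxon rank sum tests to compare the AOC in 3 different procedures in both airway providers and assistant roles". Pre- and post-doffing values are analysed separately, and procedure time is also compared by rank-sum test. No stratum or covariate is named.

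Sex enters only the secondary mixed-effect model of section 2.18, which explores whether sex, body surface area and experience influence contamination, time and first-pass success. Site enters no described analysis.

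Section 2.10 sizes the trial at 30 teams per arm for Cohen's d = 0.65, "with a significance level of 0.05, a power of 0.8" and an intra-cluster correlation of 0.7 over three scenarios. It claims no precision from stratification.

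**The concern.** Blocked allocation within strata makes the arms more alike on site and sex than simple randomisation would. The plain rank-sum test computes its null variance as if that balance had not been imposed. If site or sex predicts contamination or time, that variance is too large, the p-value tends to be too large, and between-stratum variation stays in the noise when it could be removed.

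Two things are at stake. One is power in each comparison. The other is the reading of the secondary aim: section 1.2 hypothesises no significant difference in procedure time, so a conservative test leans towards the hypothesised answer on the question of whether the box slows airway management.

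**Working it through.** **The plan's own figure.** Inputs from section 2.10: d = 0.65, alpha 0.05 (two-sided assumed, as sidedness is not stated), power 0.80, three scenarios, rho = 0.7. The mean of three correlated measures has variance factor (1 + 2 × 0.7)/3 = 0.80. Then n = 2 × 0.80 × ((1.960 + 0.842)/0.65)² = 29.7, so 30 per arm, with power 0.804. The stated size reproduces without any gain from stratification.

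**Strata.** 4 sites × 2 sexes = 8; 60/8 = 7.5 teams each, or 64/8 = 8 with the allowance for missing data.

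**Assumption.** R², the share of outcome variance explained by site and sex, is not in the documents. It is varied below.

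**Type I error by formula.** With perfect balance within strata, the true two-sided error of the unadjusted test is about 2 × (1 − Φ(1.96/√(1 − R²))):
- R² = 0.1: 1.96/0.949 = 2.066, giving 3.9%
- R² = 0.2: 1.96/0.894 = 2.191, giving 2.8%
- R² = 0.3: 1.96/0.837 = 2.343, giving 1.9%

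**Simulation, 60 teams.** Blocks of 4 within the 8 strata, normal outcome with total SD 1, one comparison, 6,000 trials per setting. Simulation error is about 0.3 points for type I error and 0.6 for power. The aligned rank test removes stratum means before ranking; the van Elteren test ranks within each stratum.

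| R² | Type I error, plain | Power at d = 0.65, plain | Van Elteren | Aligned rank |
|---|---|---|---|---|
| 0% | 5.3% | 66.4% | 60.8% | 66.0% |
| 5% | 4.9% | 66.2% | 62.9% | 67.9% |
| 10% | 3.8% | 68.5% | 66.7% | 72.1% |
| 20% | 3.3% | 67.8% | 71.0% | 76.0% |
| 30% | 2.6% | 69.2% | 76.9% | 81.5% |
| 50% | 0.8% | 69.3% | 88.6% | 92.2% |

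The type I error of both stratified tests stays between 4.6% and 5.3%. The aligned test gains 72.1 − 68.5 = 3.6, 76.0 − 67.8 = 8.2 and 81.5 − 69.2 = 12.3 points at 10, 20 and 30%. At 0% it differs from the plain test by less than the simulation error.

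**Simulation, 64 teams**, with a rank regression on arm, site and sex. At 10/20/30% the plain test has type I error 4.0/3.0/1.7% and power 70/71/73%. The regression holds 5% and reaches 74/79/84%, a gain of 4, 8 and 11 points. At 0% both have 70%.

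**Against the planned effect.** Averaging three scenarios raises the standardised effect to 0.65/√0.80 = 0.727. There the plain test has power of 77%, 78%, 79% and 80% at R² of 0, 10, 20 and 30%; the aligned test has 77%, 81%, 85% and 89%. The plain test's power does not fall as the strata become more predictive; it fails to rise as the adjusted test's does.

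**Procedure time, as illustration.** If the box had a true effect of d = 0.65 on time and R² were 20%, the chance of a non-significant result would be 100 − 68 = 32% with the plain test and 100 − 76 = 24% with the adjusted one. The documents give no effect size for time.

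**The case against.** The strongest reply is that everything depends on R². At 5% the type I error is close to nominal and the gain is about 2 points; nothing in the documents supports 20 or 30%. Section 2.18 says only that stature may matter and that the effect of sex will be explored. Section 2.1 standardises equipment, temperature and humidity across sites, section 2.2 the gowns, face shields and scenarios, and section 2.8 the photography, with contamination scaled to body surface. All of this could shrink site and stature effects. The sex stratum is that of the airway provider, with no stated link to contamination on the assistant. This stands, and it makes the point conditional.

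It may also be said that adjustment belongs in an analysis plan. That carries less weight, because the protocol itself names the test for the primary outcome and names it without strata.

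Three stronger readings might be inferred, and the documents do not support them:
- That the test is certainly too conservative. No variance share is given, and at 0% nothing is lost.
- That the trial is underpowered for this reason. Section 2.10 counts on no gain from stratifying. The power of about 66 to 71% for a single procedure arises because the sample size averages three scenarios while section 2.16 tests each procedure, which is a separate matter.
- That the trial as a whole is conservative. The effect is per test; section 2.16 implies several primary comparisons with no multiplicity rule stated, and that works in the opposite direction.

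**Conclusion.** The mismatch between stratified allocation and unstratified tests is in the protocol's own text, and its direction is clear: conservative, never inflating a single test. Its size is uncertain. If site and sex explain 10, 20 or 30% of the variance, the per-test type I error is about 4%, 3% and 2 to 2.6%, and the power forgone at d = 0.65 is about 4, 8 and 12 points; if they explain nothing, there is no cost. The figures assume normal outcomes and near-equal strata, and may be smaller for the assistant's contamination or where site standardisation works. The plan remains valid and meets its stated size without the change. This is a free improvement, of minor to moderate severity.

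**What to change.** In section 2.16, replace the plain rank-sum test for AOC and procedure time with one named rank-based analysis that has arm, site and airway-provider sex as additive terms: rank ANCOVA, or an aligned rank test. Fix the choice before unblinded data are seen.

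Do not use a van Elteren test over the 8 small strata: in the 60-team simulation it loses 5.6 points at 0% (66.4 − 60.8) and 1.8 at 10% (68.5 − 66.7), and gains only from about 20% upward. Do not use a log transform: section 2.19 reports minimal contamination with the box in preliminary work, so zero values are plausible.

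The cost is one sentence. Both factors are already recorded for randomisation, and no further teams are needed.

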### ***2.4 Protecting against sources of bias.***

It will not be possible to blind study participants to study arm allocation due to the nature of the intervention. This should not introduce a significant risk of bias as the outcome measures are highly standardized. To minimize risk of bias, the research associate conducting the photographic analysis (i.e. degree of contamination) will be blinded to study arm allocation.

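### Section 2.3 fixes a block size of 4 in a trial whose allocations site staff can see, and its envelope wording does not clearly tie each numbered package to one assignment

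*Protocol*

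**What the plan says.** Protocol section 2.3 sets out the allocation in four steps.

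- Unit: "Randomization will occur at the level of the team".
- Strata: "stratified by study site and sex of the airway provider". With four sites (section 2.1) and two sexes, this gives 8 strata.
- Sequence: "Randomization packages will be prepared at a central study site using a web-based random number generator", with allocation "conducted in blocks of 4 to ensure an even distribution of teams across study arms".
- Concealment: "Sequentially numbered recruitment packages provided for each site will contain sealed opaque envelopes (i.e. one envelope per study arm". The envelopes also carry the arm assignment and participant codes.

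On blinding, section 2.4 says: "It will not be possible to blind study participants to study arm allocation due to the nature of the intervention". The safeguard it offers is that "the research associate conducting the photographic analysis (i.e. degree of contamination) will be blinded to study arm allocation". Section 2.2 has the site investigator give hands-on feedback to the teams randomized to the box.

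The Protocol does not say who opens an envelope or when, how one envelope is picked if a package holds more than one, whether packages are numbered separately for each sex, or whether sites are kept unaware of the block size.

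**The concern.** Concealment has to stop the person enrolling a team from knowing or influencing its arm. Two features of section 2.3 weaken that.

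First, the block size is constant and written in the Protocol, and past allocations at a site are open. Anyone who keeps count can work out some of the coming assignments. Strata defined by sex give no protection, because the airway provider's sex is known before enrolment.

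Second, the parenthesis about one envelope for each arm sits badly with a centrally generated list. A list implies one assignment for each numbered package, whereas the parenthesis can be read as two.

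What is at stake is selection at entry. Section 2.5 admits attending physicians and fellows from four specialties as airway providers, and section 2.18 itself treats years of experience as a possible influence on contamination, procedure time and first-pass success. Neither specialty nor experience is a stratification factor, and the comparisons in sections 2.16 and 2.17 are rank sum tests without covariate adjustment. If stronger teams were steered to one arm, the difference would pass into the results. The blinded photographic analyst protects the measurement of contamination, not the composition of the arms.

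**Working it through.** **The Protocol's own figure.** Section 2.3 gives no computed figure. The only one nearby is the sample size in section 2.10: d = 0.65, power 0.8, correlation 0.7, 3 scenarios per team, significance level 0.05 (two-sided assumed). The variance factor is (1 + 2 × 0.7)/3 = 0.8. Then n = 2 × (1.96 + 0.84)² × 0.8/0.65² ≈ 29.7, so 30 teams per arm, as stated. Nothing below changes it.

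**Inputs for predictability.** 1:1 allocation; block of 4 (section 2.3); 64 teams recruited (section 2.10); 8 strata, so 64/8 = 8 teams or 2 blocks per stratum on average. Assumptions: complete blocks, the enroller knows the block size, and the enroller tracks past allocations within each stratum.

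**If the block list governs.** A 1:1 block of 4 has 6 equally likely sequences.

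| Place in block | Chance it is known with certainty | Chance the best guess is right |
|---|---|---|
| 1st | 0 | 1/2 |
| 2nd | 0 | 2/3 |
| 3rd | 1/3 (first two alike) | 1/3 × 1 + 2/3 × 1/2 = 2/3 |
| 4th | 1 | 1 |
| Sum | 1.333 | 2.833 |

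- Known in advance: 1.333/4 = 33.3%; 64 × 0.333 ≈ 21 teams.
- Best guess right: 2.833/4 = 70.8%; 64 × 0.708 ≈ 45 teams, against 32 by chance.

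**If each package holds both arms.** The package number does not determine the arm, and section 2.3 gives no rule for which envelope to open. The block list then does not govern, so the figures above do not apply. If instead the two envelopes were used on successive teams, the effective block would be 2, contrary to the stated 4, with 50% of assignments certain and a best guess right 75% of the time.

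**With varied blocks.** This is an exact enumeration in which the sizes are equally likely and the guesser knows the set of sizes but not their order. It was run over sequences of 8 and 16 teams.

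| Block sizes | Known with certainty | Best guess right |
|---|---|---|
| 4 only | 33.3% | 70.8% |
| 4 and 6 | 5.9-6.0% | 66.8-68.4% |
| 2, 4 and 6 | 3.0-3.6% | 68.6-69.5% |

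Over 64 teams, certain predictions fall from about 21 to about 4 (sizes 4 and 6) or about 2 (sizes 2, 4 and 6).

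**The case against.** Section 2.3 already has the main safeguards: central preparation, sequential numbering, and sealed opaque envelopes. Two stronger readings are tempting, and the text supports neither.

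- A reader might infer that packages are numbered by site only, so that the sex strata cannot be delivered. The text says that each site is provided with packages, which describes where they go. It is silent on numbering within sex, and separate series for each sex fit every word. The silence is worth closing. If one series per site were used (assuming 16 teams per site and 30-50% female providers), simulation puts the standard deviation of the between-arm difference in female providers at about 3.7-4.0, against 1.8 with true strata. The Protocol does not say that this will happen.
- A reader might infer that staff can choose the arm. That rests on one literal reading of a loosely worded parenthesis, which may only mean that a site's set covers both arms. On the literal reading the central list and the blocks would have no function. Because the envelopes are sealed and opaque, choosing would also need visible labels or the opening of more than one.

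It can also be said that envelope logistics may be left to the operating procedures promised in section 2.12, that the Protocol does not describe who schedules teams, and that the primary outcome is scored blind. Finally, setting 71% against 50% oversells the remedy, since varied blocks with a known set of sizes leave best-guess success near 67-70%.

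These points narrow the concern but do not remove it. The fixed block size is stated, site staff see allocations, and the envelope wording is unclear on the one thing it has to settle. Blinded scoring does not address selection at entry.

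**Conclusion.** The point holds in a limited form. On the reading that the central list governs, one assignment in three can be known before the team enters. This rests on the assumptions that the enroller knows the block size and follows the allocations in each stratum; without them the share is lower. On the reading that each package holds both arms, the assignment is not fixed by the list at all, but that failure cannot be sized from the Protocol. The two are alternatives and should not be added together.

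Nothing shows that any site would exploit this. The resulting bias in contamination, time or first-pass success cannot be computed from what is given; the figures measure opportunity. It is a weakness worth removing because the correction is cheap and lost concealment cannot be restored after recruitment.

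**What to change.** Reword section 2.3 to say that:

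1. each numbered package holds one sealed opaque envelope with one assignment from the central list;
2. packages run in a separate numbered series for each of the 8 site-by-sex strata;
3. the envelope is opened only after both team members have consented and been logged;
4. the list uses randomly varied block sizes (for example 4 and 6, or 2, 4 and 6), and the sizes are withheld from the sites and from documents that they hold.

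The fourth change mainly removes the certain predictions. It does little for informed guessing if the set of sizes becomes known, so the first three are needed as well.

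Cost: the central site re-prepares the envelopes, and a small arm imbalance is possible where the last block of a stratum is left incomplete.
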